### Assignment of interventions

#### Randomisation

Participant eligibility will be established before randomisation. Participants will be assigned randomly and consecutively in a 1:1 ratio to one of two interventions, NAC or placebo. The randomisation sequence will be based on a computer-generated, permutated, block randomisation scheme with stratification for site. The randomisation sequence will be computer-generated by a statistician who is independent of the day-to-day conduct of the trial. The allocation sequence will be concealed within the RPMS.

#### Blinding

This study involves a triple-blind protocol. The Investigators, the Sponsor monitor, the study’s biostatistician, research assistants, the clinical treating teams, the laboratory team and the participant will be blinded to whether the participant is receiving NAC or placebo for the duration of the trial. Unblinding will only be permitted in the case of a medical emergency when the appropriate management of the patient necessitates knowledge of the treatment randomisation. All cases of unblinding will be documented.

#### Enrolment, consent and retention

Informed, written signed consent will be obtained by a trained research assistant from all participants aged 15 to 25 years inclusive. For those individuals less than 18 years of age, written informed consent will also be required from a parent or legal guardian. Optional consent will be sought for the use of de-identified information collected during this study for future research projects, and the storage and use of blood samples for this and associated studies. The Participant Information and Consent Form will be made available by the corresponding author upon request. Once consent is acquired, the initial screening assessment will be conducted to confirm eligibility. Prior to completion of the baseline assessment randomisation will occur. The participant flow through the study is detailed in Fig. 1. At the end of the study period, clinical care will continue to be provided to participants either through EPPIC (as determined by the EPPIC eligibility criteria) or the health service to which they have been discharged. Post-trial access to NAC will not be directly provided; however, as NAC is readily available as an over-the-counter supplement, a participant may continue with NAC treatment at the end of the trial treatment period under the guidance of their treating clinician, should they wish to do so.

**Fig. 1 Fig1:**
[figure not shown]
Flow chart of study design

### Data collection, management and analysis

The majority of assessments will be administered to participants in person via a semi-structured interview; however, assessments may also be conducted over the phone, or via online video services if required. Flexibility with timing and location of assessments (e.g. home visits, after school hours, etc.) will be essential to aid in participant retention. The study team will undergo extensive training prior to completing assessments, and inter-rater reliability between raters will be established. Consent will be sought from participants for audio recordings to be made of research visits to assist in the regular assessment of inter-rater reliability of various measures over the course of the study.

Each case report file (CRF) will be regularly monitored to ensure data quality, and de-identified data will be entered into an electronic CRF embedded within Orygen’s web-based Research Project Management System. The electronic CRF data will be audited to ensure data-entry accuracy.

Study protocol, statistical analysis plan, informed consent templates and de-identified participant data will be made available to investigators whose proposed use of the data has been approved by an independent review committee, for up to 3 years following publication.

Study findings will be presented at relevant conferences and published in peer-reviewed journals. A summary of the findings will be provided to participants on request.

#### Statistical methods

Statistical analyses will follow the International Conference on Harmonisation E9 statistical principles. Reporting of results will be done in accordance with Consolidated Standards of Reporting Trials (CONSORT) guidelines [77]. All participants who were randomised and who have at least one post-baseline observation will be included in a modified intent-to-treat analysis [78]. All attempts will be made to ensure that all participants have follow-up data even if they discontinue from the treatment. The primary efficacy analysis will assess average treatment group differences for the primary outcome measure (PANSS_T_) over the entire study period and will use a likelihood-based mixed-effects model, repeated-measures approach (MMRM). The MMRM model includes the fixed, categorical effects of treatment, visit, treatment-by-visit interaction, and Region (Parkville and Sunshine) will also be included as a factor in the model. Antipsychotic dosing may be also used as the covariate in the model. The MMRM includes all available data at each time point and is the preferred method of analysing clinical trial data in psychiatry as compared to more traditional repeated measures analysis of variance and analysis of covariance models. Planned comparisons will be done with the MMRM models to determine between-group differences in change in symptom measures from baseline to week 26. Differences between treatment groups in terms of secondary outcome measures will be examined using MMRM as per the primary outcome. Correlational analyses as well as multilevel modelling will be used to develop a better understanding of how changes in blood- and brain-derived biomarkers relate to symptoms, functioning and neurocognition. No interim analyses will be conducted.

Dynamic MEGA-PRESS MRS data will be corrected for frequency drift and edit-off and edit-on spectra combined to produce a GSH-edited spectrum. Edited data will be pre-processed and fitted using the TARQUIN analysis algorithm, with the resonance at 2.9 ppm used to determine the level of GSH. Matching water-reference data will also be collected and used to determine the absolute concentration of GSH. Resting-state functional imaging data will be analysed using the GraphVar toolbox and the Automated Anatomical Labelling atlas for parcellation. To delineate the default mode network (DMN) for each participant, functional connectivity (i.e. Pearson correlation) will be computed between the signal averaged over a spherical region of interest positioned at the medial prefrontal cortex and the signal at all other brain voxels. These functional connectivity maps will be *r*-to-*z* transformed and carried forward to a second-level statistical analysis to identify significant within- and between-group differences in DMN connectivity. Factorial models similar to the MMRM approach described above will be adopted to test for main effects and interactions using the appropriate combination of *F* and *t* tests. A cluster-based permutation approach will be used to identify significant differences satisfying a family wise error rate of .05. Lastly, betweenness-centrality will be calculated for the medial prefrontal cortex nodes and correlated with GSH concentration.

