**Methods/design:**

ENACT is a 26-week, randomised controlled trial of adjunctive NAC versus placebo, with a 26-week non-treatment follow-up period, for FEP. We will be recruiting 162 young people aged 15–25 years who have recently presented to, and are being treated at, the Early Psychosis Prevention and Intervention Centre, Melbourne, Australia. The primary outcome is the Total Score on the Positive and Negative Syndrome Scale which will be administered at baseline, and weeks 4, 8, 12, 26 (primary endpoint), and 52 (end of study). Secondary outcomes include: symptomatology, functioning, quality of life, neurocognition, blood-derived measures of: inflammation, oxidative and nitrosative stress, and magnetic resonance spectroscopy measures of glutathione concentration.

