The primary aim of this randomised controlled trial (RCT) is to determine the efficacy of 26 weeks of adjunctive NAC (2 g/qds) compared to placebo as a useful treatment of psychiatric symptoms in young people (15–25 years of age, inclusive) who experience FEP. The trial agent will be adjunctive to treatment as usual (TAU) at a specialist early intervention service. A secondary aim is to explore how the multiple neurobiological mechanisms underpinning 2 g/qds NAC relate to clinical and functional outcomes following 26 weeks of adjunctive treatment with NAC, and at 52-week follow-up. Another secondary aim is to examine the relationships between gene expression and treatment response and/or medication side-effects.

The primary hypothesis is that 2 g/qds of NAC will be associated with lower total symptom severity (defined by the PANSS_T_ score) than placebo at the primary endpoint of 26 weeks. Secondary hypotheses are for the superiority of 2 g/qds NAC compared to placebo at the primary endpoint of 26 weeks and at the secondary endpoint of 52-week follow-up in terms of: (1) greater reductions in positive, negative, general and depressive symptomatology; (2) interviewer and participant ratings of clinical improvement; (3) improved global functioning and quality of life (QoL); (4) better neurocognitive functioning; (5) changes in blood-derived measures of inflammatory, oxidative and nitrosative stress; and (6) increases in brain-derived (MRS) measures of GSH concentration, and these increases will be positively correlated with changes in functional and structural connectivity of brain networks.

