## Methods/design

### Study design and ethical approval

The study design is a 26-week, parallel-group, triple-blind, randomised, placebo-controlled study in patients with a FEP, allocated to receive either 2 g/qds active NAC or matched placebo as adjunctive to TAU in a specialised early intervention service. Equal numbers of active and placebo groups will be recruited (ratio 1:1). The primary endpoint is end of treatment at 26 weeks; with a post-discontinuation follow-up at 52 weeks.

Institutional ethics and governance approval was obtained from the Melbourne Health Human Research Ethics Committee (HREC 2017.145). The study Sponsor is Orygen, The National Centre of Excellence in Youth Mental Health (referred to as Orygen). The Sponsor will not be involved in study design; collection, analysis or interpretation of data; writing of the report; and will not participate in the decision to submit the report for publication. A steering committee comprising the principal investigator, coordinating chief investigator, associate investigators, project manager, study monitor and other team members will meet on a regular basis to oversee the conduct of the trial.

The trial will be conducted in accordance with Good Clinical Practice (GCP [44];) guidelines and the Declaration of Helsinki [45]. The protocol has been developed in line with GCP and the Standard Protocol Items: Recommendations for Interventional Trials (SPIRIT) guidelines [46]. A SPIRIT Checklist is provided as an Additional file 1. The study is registered with the Australian and New Zealand Clinical Trials Registry (ACTRN12618000413224). Any amendments to the protocol will result in notifications to relevant parties including ethics, the Sponsor and trial registry.

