### Study medication

Previous studies demonstrate that a dose of 2 g/day of NAC generally appears to be effective and well tolerated [49], and the majority of studies showing efficacy of adjunctive NAC treatment for psychotic and mood symptoms have utilised a daily dose of 2 g with no significant difference from placebo in side-effect profile [37–39, 50–53]. While several studies have administered NAC in a 1-g dose twice daily [37, 39, 50], NAC will be administered as a once daily dose of 2000 mg (2 × 1-g capsules to be taken with their usual medication at the same time each day) in the current study in order to improve treatment adherence. Two previous trials by our group utilised a 24-week treatment period [37, 39]. A similar treatment period will be used in the current study though the treatment period has been extended to 26 weeks. A 26-week post-treatment follow-up will be conducted to determine whether NAC improves outcomes over the longer term. This is especially salient since the trial of NAC in schizophrenia by Brier et al. [54] showed benefits that were most robust at 9 and 12 months.

To ensure blinding, placebo capsules will be carefully matched in appearance, flavour and packaging with the active treatment. The placebo will comprise encapsulated microcrystalline cellulose. As NAC has a distinctive odour, placebo capsules will be lightly dusted with NAC powder to help prevent unblinding.

The nature of the study population is such that participants will already be taking prescribed medications. Typical treatment at EPPIC comprises low-dose SGAs. Other medications may also be prescribed in this population, e.g. mood stabilisers, anticonvulsants, antidepressants, benzodiazepines, benztropine, propranolol and non-benzodiazepine sedatives, such as zopiclone and zolpidem, will be allowed. Antipsychotic medication dosing may change during the study period and this data will be captured. Antipsychotic dosing (risperidone equivalents) will be a covariate in the analysis of impact of NAC on the primary outcome.

Study medication will be dispensed at baseline, and follow-up visits at weeks 4, 8, 12 and 18.

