#### Primary outcome

The Positive and Negative Symptom Scale (PANSS) will be used to measure overall symptom severity PANSS_T_, and severity of positive (PANSS+), negative (PANSS-) and general (PANSS_G_) psychopathology symptoms [55]. The PANSS has sound psychometric ratings in terms of both validity and reliability [56]. It has been widely used as an outcome measure in clinical trials for psychotic disorders. In the current study, change from baseline to week 26 on the PANSS_T_ score is the primary outcome measure.

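### The analysis labelled primary is an average PANSS total difference over the whole study period, but the primary outcome and hypothesis are set at week 26

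*Protocol article*

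**What the plan says.** The Statistical methods section of the protocol article defines the primary analysis in one sentence: "The primary efficacy analysis will assess average treatment group differences for the primary outcome measure (PANSS_T_) over the entire study period". The method is a mixed model for repeated measures (MMRM) with treatment, visit, their interaction and region, using all available data. Later in the same paragraph comes a second statement: "Planned comparisons will be done with the MMRM models to determine between-group differences in change in symptom measures from baseline to week 26". That sentence covers symptom measures in general and does not use the word primary.

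Elsewhere the target is week 26:

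- Abstract, Methods/design: the PANSS visits include "26 (primary endpoint), and 52 (end of study".
- Background, primary hypothesis: lower PANSS total "than placebo at the primary endpoint of 26 weeks". The secondary hypotheses there name the 52-week follow-up as a secondary endpoint.
- Study design and ethical approval: "The primary endpoint is end of treatment at 26 weeks; with a post-discontinuation follow-up at 52 weeks".
- Primary outcome: "change from baseline to week 26 on the PANSS_T_ score is the primary outcome measure".

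The Study medication section gives the later period its own question: "A 26-week post-treatment follow-up will be conducted to determine whether NAC improves outcomes over the longer term".

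**The concern.** An average of group differences over several visits and the group difference in change at one visit are different quantities. They coincide only if the effect is the same at every visit averaged. The protocol attaches the word primary to the first in the analysis section and to the second everywhere else. On the literal reading the average also brings in week 52, which the hypotheses treat as secondary and which falls 26 weeks after trial treatment ends.

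This is not detail left to a later analysis plan, because the article positively states what the primary efficacy analysis estimates. At stake is which result decides the trial: one analysis may be significant and the other not.

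**Working it through.** **1. Which visits are in the average?** Table 1 schedules PANSS total at baseline and at weeks 4, 8, 12, 26 and 52, with week 26 marked as end of treatment and week 52 as end of study. There are two readings of the study period:

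| Reading | Post-baseline visits averaged | Same as change to week 26? |
|---|---|---|
| Whole study, to week 52 | 4, 8, 12, 26, 52 | No |
| Treatment phase, to week 26 | 4, 8, 12, 26 | No |

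The mismatch with the Primary outcome section holds on both.

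**2. The plan's own figure.** Inputs from Determination of sample size: d = 0.45, power 0.80, alpha 0.05 one-tailed. n per group = 2(1.645 + 0.842)²/0.45² ≈ 61.1, so 62 per group and 124 in total, as stated. By noncentral t, 62 per group gives power 0.801 for a single contrast with d = 0.45.

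**3. Can the two analyses differ materially?** The following are assumptions, not in the document: d = 0.45 at week 26; equal visit weights; unit SD at each visit; compound symmetry with between-visit correlation ρ = 0.5 or 0.7; f = share of the week-26 effect still present at week 52. If the outcome is change from a shared baseline and the raw scores are compound symmetric, the changes correlate 0.5 whatever the raw correlation, so the ρ = 0.5 column is the one that applies there.

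SD of a k-visit average = √((1 + (k − 1)ρ)/k). For k = 5 this is 0.775 (ρ = 0.5) or 0.872 (ρ = 0.7).

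- Constant effect from week 4: average d = 0.45(4 + f)/5.
- Linear build-up to week 26: visit effects 0.45 × (4, 8, 12, 26)/26 = 0.069, 0.138, 0.208, 0.450, sum 0.865; average d = (0.865 + 0.45f)/5.

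Power by noncentral t, 62 per group, one-sided 0.05:

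| Time course | f | Average d | Power, ρ = 0.5 | Power, ρ = 0.7 |
|---|---|---|---|---|
| Constant | 0 | 0.360 | 0.823 | 0.739 |
| Constant | 0.5 | 0.405 | 0.894 | 0.823 |
| Constant | 1 | 0.450 | 0.942 | 0.887 |
| Build-up | 0 | 0.173 | 0.342 | 0.293 |
| Build-up | 0.5 | 0.218 | 0.466 | 0.398 |
| Build-up | 1 | 0.263 | 0.593 | 0.510 |
| Week 26 alone | – | 0.450 | 0.801 | 0.801 |

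On the treatment-phase reading (k = 4), power is 0.934 (0.882 at ρ = 0.7) with a constant effect. With build-up, average d is 0.216 and power is 0.448 (0.388).

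**4. How often would they disagree?** The week-26 and five-visit test statistics correlate √((1 + 4ρ)/5) = 0.775 or 0.872. Under a bivariate normal model, exactly one of them is significant in about 11–16% of trials with a constant effect and 25–51% with build-up, over both correlations and all three values of f.

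**The case against.** The best defence is that the intent is clear. Four sections fix week 26, the matching contrast is specified in the same paragraph from a model with a treatment-by-visit term, and an analysis plan not shown here may rank the two. The abstract and the design section also call this a 26-week trial, so the study period could mean the treatment phase. Much of this stands: the week-26 estimate will be produced, and the week-52 reading is the literal one but not the only one. It does not remove the contradiction, because the label primary sits on an average under either reading and the week-26 comparison is not ranked above it.

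Three stronger inferences are not supported.

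- A reader might infer that the sample size was built for week 26 and cannot serve an average. The sample-size section names no visit and starts from an effect observed over a 24-week period, so it does not discriminate between the two.
- A reader might infer that the average is the weaker test. That depends on the time course: a constant effect gives the four-visit average 93% power (88% at correlation 0.7), while build-up gives 45% (39%).
- A reader might infer an inflated error rate from a free choice of primary result. With no effect and a free choice between week 26 and the five-visit average, the one-sided error would be 7.7% (7.0%) rather than 5%. But the hypothesis and outcome sections constrain that choice, so this is a ceiling on a practice the document does not license.

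**Conclusion.** The contradiction is real and lies in current text: the analysis called primary does not estimate the primary outcome. This conclusion needs no numerical assumption and does not depend on how the study period is read. The size of the consequence does depend on assumptions. With the time courses, equal weights and correlations above, the five-visit average has about 29% to 94% power against 80% for week 26, and the two tests disagree in roughly 11% to 51% of trials. These figures show that the choice matters, not which way it would go. The point should be corrected before unblinding. It is no threat to the design, since the intended endpoint is plain elsewhere and the model already yields it.

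**What to change.** In Statistical methods, replace the sentence on the average over the study period with one naming the MMRM treatment contrast for change from baseline to week 26 in PANSS total as the single primary efficacy analysis. Keep all visits in the model. List the week-52 contrast as secondary, and the period average too if it is kept. This brings the section into line with the primary hypothesis, the design section and the outcome definition.

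The cost is a sentence or two, with no new data, visits or participants; the stated 62 per group still gives 80% power at d = 0.45. The downside is some lost power if the effect appears early and lasts: 80% for week 26, against 94% (89% at correlation 0.7) for the five-visit average with a constant, fully sustained effect.

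### The primary efficacy analysis is defined as an average PANSS total difference over the study, but the primary endpoint, hypothesis and outcome are all set at week 26

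*Protocol article*

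**What the plan says.** Four places in the protocol article put the primary question at week 26:

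- Abstract, Methods/design: PANSS is "administered at baseline, and weeks 4, 8, 12, 26 (primary endpoint), and 52 (end of study".
- Background, final paragraph: the primary hypothesis is "lower total symptom severity (defined by the PANSS_T_ score) than placebo at the primary endpoint of 26 weeks".
- Study design and ethical approval: "The primary endpoint is end of treatment at 26 weeks; with a post-discontinuation follow-up at 52 weeks".
- Primary outcome: "change from baseline to week 26 on the PANSS_T_ score is the primary outcome measure".

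Statistical methods then gives the task of the primary efficacy analysis as assessing "average treatment group differences for the primary outcome measure (PANSS_T_) over the entire study period". The model is an MMRM with treatment, visit, treatment-by-visit interaction and region. Later in the same paragraph comes: "Planned comparisons will be done with the MMRM models to determine between-group differences in change in symptom measures from baseline to week 26". That comparison covers symptom measures in general and is not called primary. Secondary outcomes are to be analysed in the same way as the primary outcome.

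**The concern.** The article gives the label primary to two different quantities. One is the between-group difference at the end of treatment. The other is a difference averaged over visits, which mixes the early visits with the end of treatment and probably with a visit 26 weeks after trial medication stops. The two coincide only if the treatment effect is the same at every visit included. The protocol gives no ground for presuming that: Study medication cites an earlier NAC trial in schizophrenia in which benefit was strongest at 9 and 12 months.

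A statistician who follows Statistical methods literally would test something other than the stated hypothesis. The average could be significant and the week-26 contrast not, or the reverse, and a report could point to the text for either. The conflict also carries over to the secondary outcomes, whose hypotheses are set at weeks 26 and 52 separately.

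**Working it through.** **1. Which visits enter the average.** Table 1 schedules PANSS at baseline and weeks 4, 8, 12, 26 and 52.

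- If the study period ends at week 52, which the abstract and Table 1 label the end of study, the average covers five post-baseline visits, the last one off treatment.
- If it ends at week 26, the average covers four visits.

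Neither average is the week-26 change.

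**2. The plan's own sample size.** Inputs from Determination of sample size: d = 0.45, one-tailed alpha 0.05, power 0.80.

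n per group = 2(1.645 + 0.842)² / 0.45² = 61.1, rounded up to 62, or 124 in total. This reproduces the stated figure. Power at 62 per group is Φ(0.45 × √(62/2) − 1.645) = Φ(0.861) = 0.805 (0.801 with the noncentral t). This is the figure for a single contrast such as week 26.

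**3. How far the average can differ (illustration only).** The document gives no effect profile, no between-visit correlation and no weights. The assumptions are:

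- equal visit weights;
- SD 1 at each visit;
- compound-symmetric correlation ρ from 0.4 to 0.7;
- 62 per group at every visit.

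The variance of a k-visit mean is [1 + (k − 1)ρ]/k. Power is Φ(δ/SD × √31 − 1.645), where δ is the averaged effect and SD the square root of that variance.

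Two profiles reach 0.45 at week 26. One rises linearly: 0.45 × 4/26 = 0.069, 0.45 × 8/26 = 0.138, 0.45 × 12/26 = 0.208, then 0.45. The other is 0.45 from week 4 onwards.

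Example: linear rise, no effect at week 52, ρ = 0.5. δ = (0.069 + 0.138 + 0.208 + 0.45 + 0)/5 = 0.173. The variance is (1 + 4 × 0.5)/5 = 0.6, so SD = 0.775 and δ/SD = 0.223. Power = 0.344.

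| Profile | Visits averaged | δ | Power, ρ = 0.4 | ρ = 0.5 | ρ = 0.7 |
|---|---|---|---|---|---|
| Linear rise, week 52 = 0 | 5 | 0.173 | 0.379 | 0.344 | 0.295 |
| Linear rise, week 52 = 0.225 | 5 | 0.218 | 0.516 | 0.469 | 0.400 |
| Linear rise, week 52 = 0.45 | 5 | 0.263 | 0.650 | 0.597 | 0.514 |
| Linear rise | 4 (to week 26) | 0.216 | 0.492 | 0.452 | 0.391 |
| Constant, week 52 = 0 | 5 | 0.360 | 0.872 | 0.827 | 0.744 |
| Constant to week 52 | 5 | 0.450 | 0.966 | 0.944 | 0.890 |
| Constant | 4 (to week 26) | 0.450 | 0.959 | 0.936 | 0.885 |

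In every row the week-26 effect is 0.45 and its power 0.805. The four-visit row under a linear rise shows that dropping week 52 does not remove the discrepancy: 0.216/0.45 = 48% of the week-26 effect.

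**The case against.** The strongest defence is that the intention can be recovered. Four places agree on week 26, one sentence is out of line, the model contains the treatment-by-visit term, and the week-26 comparison is already planned. A separate statistical analysis plan is mentioned and may settle the order. All this stands, and it makes the correction cheap. It does not remove the defect: the sentence states positively that a different quantity is the primary efficacy analysis, so this is a contradiction and not detail left to another document.

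A reader might also infer four stronger points, which the document does not support as they stand:

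- **That week 52 is certainly in the average.** Statistical methods lists no visits, and Study design calls the trial a 26-week study. Inclusion of week 52 is the more natural reading, but it is an inference.
- **That the average loses power.** The illustration falls on both sides of 0.805 and depends wholly on assumptions. It also holds 62 per group at every visit, whereas the mixed model uses all available data, so early visits could contribute participants who leave later.
- **That the sample size cannot apply to the average.** Determination of sample size names no visit for d = 0.45. Linking it to week 26 is reasonable, but the section does not do so.
- **That NAC use after week 26 is part of this contradiction.** Enrolment, consent and retention does say "a participant may continue with NAC treatment at the end of the trial treatment period". But calling the follow-up non-treatment can fairly mean that the trial supplies none, and concomitant medication is reviewed at weeks 27, 36 and 52. This bears on how to interpret week 52, and the correction does not depend on it.

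**Conclusion.** The contradiction holds on the wording alone and needs no assumption: the primary efficacy analysis, as defined, does not estimate the quantity named in the primary hypothesis and primary outcome. This is so whether the average ends at week 26 or at week 52.

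The numerical consequence is not determined by the document. Under the assumed profiles and correlations the averaged effect lies between 0.173 and 0.45 SD and its power between about 0.30 and 0.97, against 0.45 SD and 0.805 for week 26. These figures show only that the two analyses can diverge in either direction. They are not a forecast of lost power. The primary test should be settled before unblinding, because it decides whether the trial is read as positive.

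**What to change.** In Statistical methods, replace the sentence defining the primary efficacy analysis with wording such as: *The single primary efficacy analysis is the NAC-minus-placebo difference in change in PANSS total from baseline to week 26, estimated as the week-26 treatment-by-visit contrast from the MMRM. Any average over visits, and the difference at week 52, are separate secondary contrasts.* If an average is kept, name its visits and weights. Bring the statistical analysis plan into line if it does not already say this.

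The cost is one sentence, plus the amendment notices to ethics, sponsor and registry that the article already provides for. No new data, visits or model terms are needed. The evaluable sample size of 124 is unaffected, since the stated calculation fits a single week-26 contrast as written. The study biostatistician is blinded and no interim analysis is planned, so the change can be made without knowledge of the results.

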### Determination of sample size

Previously, moderate effects have been observed (Cohen’s *d* = 0.57) in those who received NAC on global symptom outcomes over a 24-week period [37]. We have elected to use a conservative estimate of effect of 0.45 (Cohen’s *d*) for between-group differences on the PANSS_T_ score. With power (1 − β) set at 0.80, alpha (α) set at .05, and a one-tailed test we would need a total sample size of 124 (62 per group). Allowing for attrition rate of 30%, we calculate that we would need a total sample size of 162 (81 per group).

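### The primary MMRM, as listed, omits baseline PANSS total while its week-26 contrast is change from baseline: valid, but less precise than it could be at no cost

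*Protocol article*

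**What the plan says.** In the Protocol article, Statistical methods, the primary model is set out term by term: "The MMRM model includes the fixed, categorical effects of treatment, visit, treatment-by-visit interaction, and Region (Parkville and Sunshine"). One covariate is then mentioned, as optional: "Antipsychotic dosing may be also used as the covariate in the model". Baseline PANSS total appears in neither place.

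Under Primary outcome, "change from baseline to week 26 on the PANSS_T_ score is the primary outcome measure". Statistical methods takes from the MMRM planned comparisons of "between-group differences in change in symptom measures from baseline to week 26". The same section also describes the analysis more broadly: "The primary efficacy analysis will assess average treatment group differences for the primary outcome measure", taken over the whole study period.

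The sample size section uses a "conservative estimate of effect of 0.45" (Cohen's d) without saying which standard deviation it is scaled to, and plans a "one-tailed test we would need a total sample size of 124 (62 per group"), raised to 162 for 30% attrition.

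On the order of events, Enrolment, consent and retention says: "Prior to completion of the baseline assessment randomisation will occur". Table 1 places randomisation and the baseline PANSS in the same visit window (day -7 to 1).

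**The concern.** Baseline PANSS total is collected on the same scale as the outcome and would normally be among its better predictors. A model with treatment, visit, their interaction and region, read out as a difference in change, subtracts the whole baseline value instead of the fraction that predicts the outcome. Whenever the correlation is below 1, that adds avoidable noise. Randomisation is stratified by site only, so the design does nothing else to balance baseline severity. What is at stake is power and the width of the confidence interval in a trial sized at 80% power.

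A smaller matter is that change from baseline relies on a baseline fixed before allocation. The article does not explicitly guarantee that for the PANSS.

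**Working it through.** **Inputs from the article.** d = 0.45, one-tailed alpha 0.05, power 0.80, 62 per group evaluable, 81 per group randomised, 30% attrition, 1:1 allocation.

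**Assumed.** The correlation rho between baseline and week-26 PANSS total is not in the article; I use 0.3, 0.5 and 0.7. I also assume equal variances at the two visits.

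**The plan's own figure.** n per group = 2(1.645 + 0.842)²/0.45² = 61.1, so 62 per group and 124 in all. The noncentral t also gives 62 (power 0.801). 124 × 1.3 = 161.2, giving 162. Losing 30% of 162 leaves 113.4, or 56.7 per group.

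**Variance of the week-26 contrast, complete data** (in units of the raw variance):
- change score: 2(1 − rho)
- baseline-adjusted: 1 − rho²
- ratio, adjusted to change: (1 + rho)/2

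| rho | change | adjusted | ratio |
|---|---|---|---|
| 0.3 | 1.40 | 0.91 | 0.65 |
| 0.5 | 1.00 | 0.75 | 0.75 |
| 0.7 | 0.60 | 0.51 | 0.85 |

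**Does an MMRM with baseline as one of the visits already recover this?** A generalised least squares calculation was run with baseline and weeks 4, 8, 12 and 26 as responses and the same correlation rho between all visits. With treatment-by-visit free at baseline, the variances are 1.40, 1.00 and 0.60, identical to the change score. With the baseline mean held equal across arms, they are 0.91, 0.75 and 0.51. The gain comes from the constraint (or the covariate), not from using an MMRM.

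**With dropout.** Assume 10% are lost after each of weeks 4, 8 and 12, so 70% reach week 26. Per 81 randomised per arm, the variances are 1.756 against 1.266, 1.268 against 1.018, and 0.767 against 0.677. The ratios are 0.72, 0.80 and 0.88.

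**Power, one-tailed, 56.7 completers per group (noncentral t).**
- If d = 0.45 is on the raw SD, the standardised effect is 0.45/√(2(1 − rho)) for change and 0.45/√(1 − rho²) for adjusted. Power goes from 0.64 to 0.80 (rho 0.3), 0.77 to 0.87 (rho 0.5) and 0.92 to 0.95 (rho 0.7).
- If d = 0.45 is on the change-score SD, the unadjusted power is 0.77 throughout, and the adjusted effect is 0.45/√((1 + rho)/2) = 0.558, 0.520 and 0.488. Power becomes about 0.91 (0.905 by noncentral t, 0.908 by normal approximation), 0.87 and 0.83.

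**Power using partial data as well.** The MMRM also uses people who drop out. Taking the dropout variances above, d on the raw SD and a normal approximation, power = Φ(0.45/√(2V/81) − 1.645). This gives 0.70 to 0.82, 0.82 to 0.88 and 0.95 to 0.97, a somewhat smaller gain than for completers alone.

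**The case against.** **The article is condensed and an analysis plan exists.** The list is of categorical effects, and baseline PANSS is continuous, so its absence does not prove exclusion. This stands in part: the supportable statement is that baseline is not listed. But the article goes on to name a covariate, and it names only antipsychotic dosing. It specifies the model rather than leaving it open.

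**A change contrast is legitimate.** This stands. A reader might infer that the estimate is biased by chance baseline differences. It is not: over repeated randomisation the contrast is unbiased, and its standard error already reflects that variation. The loss is one of efficiency.

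**The size is uncertain.** This also stands. Rho is not given, and at 0.7 the gain is only a few points of power. A reader might quote far lower power by computing two-sided, but that is not the planned test. Nor may one reading of d be taken as settled. The absence of PANSS entry limits does not strengthen the case: other things equal, a wider baseline range raises rho and so shrinks the loss.

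**The ratios apply only to the week-26 change contrast.** This is correct. The article also describes an average over the study period, and the two descriptions need reconciling.

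**Order of randomisation.** A reader might infer that PANSS is rated after allocation. The sentence concerns the baseline assessment as a whole, which includes cognition, bloods and imaging, and does not name PANSS. Allocation is concealed, raters and participants are blinded, and the placebo is matched. Bias is unlikely.

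**Conclusion.** The point holds as one of efficiency and should be acted on. As listed, the primary model leaves out baseline PANSS total, and its week-26 contrast has more variance than necessary. Adjustment brings that variance to 65–85% of its value with complete data, or about 72–88% with 30% monotone dropout, over assumed correlations of 0.7 down to 0.3 (the larger reduction at the lower correlation). The gain in one-tailed power for about 113 completers ranges from roughly 3 to 16 percentage points if d is on the raw SD, and from roughly 6 to 14 if it is on the change-score SD.

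These figures rest on the assumed rho, equal variances across visits, the assumed dropout pattern, and the model being as listed. An unseen analysis plan may already add the term. The direction does not depend on the value of rho, nor on whether the response is change or raw score with baseline as an unconstrained visit. The documents do not support a claim of bias. The randomisation-order wording is a minor gap in the text, not evidence of a fault in the data.

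**What to change.** - Before unblinding, add baseline PANSS total and baseline-by-visit as covariates in the primary MMRM. Alternatively, keep baseline in the response vector with a common baseline mean for both arms.
- Do the same for each secondary scale that has a baseline measurement, using its own baseline.
- State whether d = 0.45 refers to the raw or the change-score SD, and reconcile the week-26 contrast with the whole-period average.
- For participants still to be enrolled, state that the baseline PANSS is rated before allocation. Bloods and scans need not be reordered for this purpose.

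The cost is wording in the analysis plan and protocol, and possibly a small change in the order of the baseline visit. No new data or participants are needed. Recruitment began in December 2018, so the order of events cannot be changed for those already enrolled, but the model change applies to everyone.
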